## Abstract

**Background:**

Late life depression (LLD), a common mental disorder, has become an increasingly acute public health concern with a quickly expanding geriatric population worldwide. To our knowledge, however, the incidence of LLD in northern cities in China has not been empirically investigated, and many elderly people with depressive moods and mild depressive symptoms have not been given sufficient attention.

**Methods/Design:**

This is a multi-stage and prospective study. The first stage is a cross-sectional study, investigating the epidemiological characteristics of LLD in northern China and exploring the biological, psychological, and social risk factors for developing LLD based on a set of questionnaires from 6,800 community-residing elderly adults. The second stage involves statistical analysis, by constructing a risk factor model for LLD and analyzing their direct and indirect functional routes on the basis of structural equation modeling. The third stage is an experimental study a total of 60 elderly patients with LLD and their principle caregivers will be randomly assigned to control and trial groups. The trial group patients and caregivers will undergo supportive psychosocial, drug treatment, and health education (PDH) intervention, whereas the control group patients and caregivers will be treated routinely (treatment as routine, TAR, which includes drug treatment and health education). At the end of the intervention, depressive symptoms, quality of life, and the social and cognitive functioning of the patients in the two groups will be respectively assessed at a baseline and after 6, 9, and 12 months post-intervention by employing scales and questionnaires to analyze the effectiveness of the supportive PDH intervention measures in comparison with TAR. Ultimately, a supportive PDH intervention and health management model will be obtained by combining PDH intervention with mental health institutions, community health services, and aging families as the main line.

**Discussion:**

This study will provide strong and suitable evidence for enhancing the integrated supportive PDH intervention and health management model of LLD patients among community-dwelling residents.

**Ethics:**

This study has been approved by the Ethics and Research Committee of the First Affiliated Hospital of China Medical University (approval No. [2019] 2019-312-2).

## Introduction

Late life depression (LLD) is complex, burdensome, and difficult to treat. Specifically, it refers to elderly people who, for the first time in their lives, meet criteria for major depressive disorder (MDD) or display clinically significant depressive symptoms such as functional disability, cognitive decline, increased risk of medical comorbidity (e.g., co-dementia), and even suicide in severe cases (1–4). Meanwhile, MDD in the elderly, as defined by the Diagnostic and Statistical Manual of Mental Disorders, Fourth Edition, Text Revision (DSM-IV TR), has been a growing public health concern, and it is projected to be the second leading cause of disease by the year 2020 (5, 6). Epidemiological surveys reported the prevalence of MDD in elderly adults in different countries, such as the USA at 16% (7), England at 8.7% (8), and India at 24.1% (9), with considerable regional variation. Additionally, the results of a meta-analysis based on 28 studies and 76,432 subjects showed that the point, 12-month, and lifetime overall prevalence of MDD in elderly adults was, respectively, 2.7%, 2.3%, and 2.8% in China (10).

Evidence shows that successful antidepressant treatment is one of the most effective ways of reducing disability, preventing morbidity, and improving quality of life (QOL) in older patients (11). However, the response rate to an antidepressant trial with adequate dose and duration is often inadequate, and can be as low as 30%~40% in LLD patients (12). Moreover, studies have found that it is difficult to improve the cognition and personality traits of elderly patients with pharmacotherapy alone, and a number of adverse events (e.g., cardiovascular, gastrointestinal, and anticholinergic complications) are often associated with antidepressant use. Frequently, this leads to discontinuation, which contributes to a high recurrence rate and mortality (13, 14). Thus, various forms of non-pharmacological therapies with negligible side effects are being embraced by patients, such as meditation, motor therapy, cognitive behavioral therapy, interpersonal psychotherapy, reminiscence therapy, alternative therapies, and group or educational activities (15–19). These treatments are tailored to the abilities of elderly patients and target multiple contributing factors with the aim of alleviating loneliness and comorbid anxiety, enhancing social support, and improving QOL.

In Western countries in the 1970s, health management, an important topic in the field of healthcare, developed rapidly and was successfully implemented for chronic conditions such as hypertension, diabetes mellitus, and chronic obstructive pulmonary disease (20–22). By combining information technology, geriatric medicine, and community medicine, health management has been used to strengthen the management of chronic diseases in the elderly, improve their lifestyle, and reduce mortality rates from disease (23). In China, relevant documents promulgated by the Chinese State Council clearly stated that health management is a fundamental way to improve the health quality of the elderly, extend life expectancy, and achieve healthy aging. However, there are few studies on community-based health management of patients with LLD, even though it is imperative to develop health management services for the elderly in the field of gerontology.

According to literature review and analysis, we found that there are four main deficiencies of the existing research. First, due to a large elderly population base, rapid aging growth, uneven distribution of mental health resources, and insufficient public attention to the mental health of the elderly, under-recognition and under-treatment of depression appears to be severe in Liaoning which ranked first among 19 provinces and cities in terms of the proportion of the elderly population aged 65 and above in 2016. Second, research on interventions for LLD is limited. Previous studies have been mostly based on pharmacotherapy, psychosocial intervention, health education, or a combination of any two of these, but none, to our knowledge, have been conducted combining all aspects together. Third, research on the risk factors of LLD has been limited, and the methods used have not been sufficiently systematic. Previous studies were limited to investigating risk factors (24–26), but lacked any discussion of the internal relations among the various factors. As such, they were limited with regard to providing guidance based on their results and conclusions for the treatment and intervention of diseases. Fourth, there is a lack of systematization and wholeness in research on the intervention of LLD. Previous studies mostly focused on tests of intervention methods. Due to impoverished intervention resources, objectives, and effects, and intervention objects and their background environment, intervention measures often have poor extensibility and cannot be repeated to verify research results. Here, we will comprehensively analyze the risk factors leading to LLD in Liaoning province, and construct integrated supportive PDH intervention and health management model of LLD patients among community-dwelling residents, aiming to provide scientific evidence for the implementation of interventions and health management, as well as formulation of relative health policies.

## Objectives

This study is designed to comprehensively assess the overall community mental health resources available to LLD patients, along with the prevalence, risk factors, and prevention and treatment status of LLD in Liaoning. By exploring and constructing the integration of psychosocial interventions, medical care, and health education with psychiatric hospitals, community health services (CHS), and aging families, this study can provide a reference for the practice of supportive intervention and health management, as well as guidance for formulating health policies in Liaoning. The aims of this study are as follows:

Analyze the epidemiological characteristics of LLD in Liaoning province.Construct a risk factor model for LLD in Liaoning.Conduct supportive psychosocial, drug treatment, and health education (PDH) interventions alongside treatment as routine (TAR) in a trial group and control group, respectively, to compare their effectiveness with regard to patients and their caregivers.Establish a supportive PDH intervention and health management (SIHM) model for elderly patients with depression according to the local economic level, mental health resources, and demographics of Liaoning.

## Methods/Design

### Organizational Structure

Team members of the preliminary investigation will consist of six graduate students studying psychiatry, two clinical psychiatrists with experience in the fields of mental health, geriatrics, and medical psychology, and five CHS staff members from Liaoning province. Before implementing the questionnaire survey, graduate students and CHS staff will undergo unified training, to explain the specific purpose, content, significance, procedures, and principles of the investigation. Further, the team members will learn the definitions and scoring criteria of each item in the questionnaires and scales, communication skills for interacting with elderly patients and their caregivers, and possible problems and solutions that might be encountered. After sampling according to inclusion and exclusion criteria, the psychiatrists, accompanied by other team members, will enter selected communities, ask permission from community leaders, and complete the investigation in public activity areas or at elderly residences accompanied by the arranged community staff.

In addition, team members of the intervention will comprise graduate students in psychiatry, one clinical psychiatrist, and one psychologist employed to supervise and guide the intervention process. After team members work out a detailed intervention plan according to the purpose of the project and the characteristics of the research objects, the research team will organize experts in psychiatry, psychotherapeutics, social medicine, and geriatrics to review and approve the plan. Afterwards, the plan will be revised and improved based on expert advice before implementation. Then, in the course of carrying out the plan, the intervention team members will record any problems with the intervention process and immediately report back to the project leader for revisions before further implementation. The goal of such cycles is to ensure the effectiveness of the intervention.

### Quality Control

In order to ensure the quality of the preliminary investigation of this project, we formulated the following measures. First, there will be unified training for researchers before data collection to reduce bias caused by differences among researchers. Second, when carrying out the questionnaire, the environment will be as quiet as possible, so as to facilitate the emotional stability of the research subjects and avoid adverse effects from the internal and external environment. Third, when collecting the questionnaires after completion, missing items will be promptly identified (without violating the principle of voluntariness) to ensure the accuracy and integrity of the survey data. Finally, data obtained from the survey will be input into statistical software for analysis by two investigators working together. At the same time, before statistical processing, SPSS descriptive statistics will be used to verify the recorded data, and errors will be corrected.

Similarly, the following three measures were developed to ensure the quality of the intervention. First, members of the intervention team will regularly report the concrete content of the intervention measures and the implementation process to the project leader and clinical psychiatrists. Second, a clinical psychiatrist will be invited to evaluate, guide, and correct the accuracy of the intervention measures and methods, along with any problems with the intervention and suitable solutions. Third, contingency plans will be developed and imparted to researchers in case of any emergencies while executing intervention measures.

### Study Design

This is a multi-stage and prospective study. It includes the following three stages:

The first stage is a cross-sectional study, based on the baseline information from 6,800 community-dwelling elderly adults collected through a set of questionnaires. The aim of the first stage is to investigate the epidemiological characteristics of LLD in northern China, and to explore the biological, psychological, and social risk factors for developing LLD.The second stage involves statistical analysis, with the aim of constructing a risk factor model for LLD and analyzing direct and indirect functional routes on the basis of structural equation modeling (SEM).The third stage is an experimental study, comprising a 6-month supportive intervention period and a 6-month follow-up period. In order to ensure the participation of the subjects in this study and improve the effectiveness of the interventions, a total of 60 elderly patients with depression and their principle caregivers will be randomly and equally assigned to trial and control groups.

Trial group patients and caregivers will undergo supportive PDH interventions, and control group patients and caregivers will receive TAR. Subsequently, depressive symptoms, QOL, and the social and cognitive functioning of the patients in the two groups will be respectively assessed at a baseline and after 6, 9, and 12 months post-intervention by using scales and questionnaires to analyze the effectiveness of the supportive PDH intervention measures. Ultimately, an SIHM model will be constructed by combining PDH intervention with mental health institutions, CHS, and aging families as the main line.

### Participants

We plan to enroll the participants between December 2019 and December 2022. The goal is to recruit 6,800 community-residing elderly adults to complete the baseline investigation. Then, 60 LLD patients who meet more strict criteria, along with their principle caregivers, will receive 6 months of supportive PDH intervention followed by a 6-month follow-up period. The inclusion and exclusion criteria for all the respondents, patients with LLD, and caregivers are listed in **Table 1**.

**Table 1 T1:** Inclusion and exclusion criteria for community-residing elderly adults in rural and urban cites/villages in Liaoning province.

Research subjects	Inclusion criteria	Exclusion criteria
6,800 community-residing elderly adults	aged 60 years old or above at the time of enrollment; permanent urban/rural community-dwelling residents (at least 5 years of residency) with urban/rural *hukou* status in Liaoning province; comprehension, reading, and writing skills to independently complete the questionnaires/scales or complete them with the assistance of the researchers without obstacles; voluntary participation and signed informed consent.	serious health concerns, such as acute infectious diseases, unstable cardiovascular disease, etc.; lifetime substance or alcohol dependence; high suicide risk; met criteria for dementia (major neurocognitive impairment in DSM-5); in the process of a depressive episode; former permanent urban/rural community-dwelling resident that has been away for 1 year or more.
60-LLD patients	aged 60 years old or above at the time of enrollment; permanent urban/rural community-dwelling residents (at least 5 years of residency) with urban/rural *hukou* status in Liaoning province; meet diagnostic criteria for MDD without psychotic features based on the Chinese version of MINI according to DSM-IV TR (the core diagnostic criteria of the symptomatology and course of disease are consistent with DSM-5). comprehension, reading, and writing skills to independently complete the questionnaires/scales or complete them with the assistance of the researchers without obstacles; voluntary participation and signed informed consent.	1) serious health concerns, such as acute infectious diseases, unstable cardiovascular disease, etc.; lifetime substance or alcohol dependence; high suicide risk; met criteria for dementia (major neurocognitive impairment in DSM-5); in the process of a depressive episode; former permanent urban/rural community-dwelling resident that has been away for 1 year or more.
60-principle caregivers	assumes most of the responsibility of caring for the patient (e.g. daily care, accompanying the patient to medical treatment, etc.) no communication barriers; voluntary participation and signed informed consent.	caregiver who receives remuneration; history of any psychiatric disorder; suffers from diagnosed organic or psychiatric disease (e.g., depression); refuses to provide authentic and reliable information to the research team.

LLD, late life depression; MINI, mini-international neuropsychiatric interview; DSM-IV TR, Diagnostic and Statistical Manual of Mental Disorders, Fourth Edition, Text Revision; MDD, major depressive disorder.

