### Data Preprocessing and Statistical Analysis

The statistical analyses will be performed by employing the SPSS statistical package, version 20.0 (SPSS Inc., Chicago, IL, USA), and all evaluations of significance will be determined based on two-sided tests using the 0.05 level of statistical significance. In addition, missing values will be replaced by the column mean/median in this study. The details of the analytic approach are as follows.

Demographic and clinical characteristics, lifestyle patterns, medical history, history of alcohol and drug abuse or dependence, family history of mental illness, self-knowledge and treatment attitude, and the self-efficacy levels and depressive symptoms of the subjects will be described by frequency distribution, percentage, arithmetic mean, and standard deviation.Comparison of the above variables between patients with or without LLD will be made using the independent-sample *t*-test, Mann–Whitney *U*-test, and the chi-squared test, as appropriate.Correlation analysis, logistic regression (for binary variables), and multiple linear regression (ANCOVA for continuous variables) will be used to determine whether the variables can enter SEM, and to test the direct and indirect pathways among these hypothesized determinants.Amos version 22.0 statistical software will be used for SEM of the risk factors for LLD.GDS, SDSS, SF-36, OPQOL, Family APGAR, GSES, IBS, MoCA, and the related KAP for LLD in the elderly will be used as evaluation indices, and analysis of variance (ANOVA) will be applied to compare the results of the control and the trial groups before and after intervention.Regression analysis will be used to analyze the influence of various factors on the effectiveness of the supportive PDH intervention.

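### The 6,800-person survey reuses the trial's exclusions for high suicide risk and lifetime dependence, which conflicts with its aims of estimating prevalence and modelling risk factors

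*Protocol article*

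**What the plan says.** The Objectives section of the protocol article sets out to assess "prevalence, risk factors, and prevention and treatment status of LLD in Liaoning". The section on sample size names the epidemiology and the risk model as the primary goals.

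In Table 1 (Participants), the exclusions for the 6,800 survey respondents include "lifetime substance or alcohol dependence; high suicide risk; met criteria for dementia". The row for the 60 trial patients carries the same items: "lifetime substance or alcohol dependence; high suicide risk; met criteria for dementia (major neurocognitive impairment in DSM-5); in the process of a depressive episode". The text above the table nevertheless speaks of "60 LLD patients who meet more strict criteria". The extra strictness lies only in the added diagnostic inclusion criterion; the two exclusion lists match.

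Two other places bear on this:

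- The Introduction describes LLD as bringing "increased risk of medical comorbidity (e.g., co-dementia), and even suicide in severe cases".
- Data Preprocessing and Statistical Analysis lists, among the variables to be described, "medical history, history of alcohol and drug abuse or dependence, family history of mental illness". The next item compares the listed variables between people with and without LLD, and the one after that screens variables for the structural equation model.

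No section limits the prevalence target to people without these conditions. The Discussion presents the sample as inclusive and representative, and its list of limitations does not mention these exclusions.

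**The concern.** Exclusions that may suit a treatment trial have been carried into a survey whose purpose is to count cases and explain them. Two of them act against that purpose.

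- **High suicide risk.** The Introduction attributes suicide to severe LLD, so this exclusion selects on a feature of the outcome. If cases are excluded more often than non-cases, measured prevalence is too low. The cases left for the risk model also lack their severe end.
- **Lifetime substance or alcohol dependence.** The analysis plans to compare a history of abuse or dependence by LLD status, but eligibility removes everyone with dependence before the comparison is made.

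The result would be reported as the prevalence in Liaoning, although it describes a narrower population. This is separate from the exclusion, in the same row, of people in a current depressive episode. Correcting that item alone would leave these two in place.

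**Working it through.** **Inputs.** All are from the section on sample size: planning prevalence P = 2.8%, α = 0.05, relative error 0.15P, N = 6179 before missing data, and 6,800 after a 10% allowance.

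**The plan's own figure.** N = z²P(1−P)/(0.15P)².

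- With z = 1.96 and P = 0.028: 3.8416 × 0.028 × 0.972 / 0.0042² = 5927, about 4% below the stated 6179.
- With z rounded to 2: 6171. With P = 2.7% (the point prevalence in the Introduction) and z = 1.96: 6153. Either variant comes close to 6179.
- 6179 × 1.10 = 6797, rounded to 6,800.

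The present point does not depend on which variant was used. What matters is that the 15% describes random sampling error only. At N = 6179 and P = 2.8% the relative half-width is 1.96 × √(0.028 × 0.972/6179)/0.028 = 14.7%.

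**Bias from the suicide-risk exclusion.** Let f be the share of cases excluded and g the share of non-cases excluded. Among those enrolled:

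p_obs = P(1−f) / [P(1−f) + (1−P)(1−g)]

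If f = g there is no bias, and if f > g the bias is downward. The sample size does not appear in the formula, so recruiting more people changes nothing. The documents give neither f nor g; every value below is an assumption.

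| f | g | p_obs | Relative bias |
|---|---|---|---|
| 5% | 0 | 2.66% | −4.9% |
| 10% | 0 | 2.53% | −9.7% |
| 15% | 0 | 2.39% | −14.6% |
| 20% | 0 | 2.25% | −19.5% |
| 10% | 3% | 2.60% | −7.0% |
| 20% | 3% | 2.32% | −17.1% |

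Worked line for f = 10%, g = 0: 0.0252/(0.0252 + 0.972) = 0.02527, and 0.02527/0.028 − 1 = −9.7%.

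**Dependence.** No arithmetic is needed. Table 1 fixes lifetime dependence at zero among both LLD and non-LLD respondents, so its association with LLD cannot be estimated. The planned variable also covers abuse, which Table 1 does not exclude. It is therefore truncated to, at most, its abuse component.

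**Availability of the data.** Table 3 gives the MINI to all 6,800 at screening, and Data Collection says that it is used for substance and alcohol disorders and other possible exclusions. The two excluded features are thus to be ascertained at an interview that already takes place.

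**The case against.** The strongest reply has five parts.

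1. **The history variable is not emptied.** This stands. A reader might infer that the exclusion removes a listed risk factor altogether, leaving nobody exposed. The documents do not support that, because abuse without dependence remains eligible under Table 1. Only the dependence contrast is lost.
2. **The size is assumed.** This also stands. A reader might infer that the bias exceeds the plan's 15% tolerance. No exclusion rate is given, losses of 5% to 10% of cases give a bias below 15%, and the 15% is a precision target rather than an allowance for bias. The direction, given f > g, needs no such assumption.
3. **Other associations.** It is tempting to add that associations with life events, coping style or lifestyle are attenuated. The exclusion applies to cases and non-cases alike, and nothing in the documents fixes the size or direction of that effect. Only the loss of the severe end of the cases can be claimed.
4. **The depressive-episode exclusion in the same row is worse.** Read literally it removes all current cases, and until it is resolved this point adds little to the loss of current prevalence. But it is a different defect, and this one remains once it is corrected.
5. **Dropping the exclusions is not the only remedy.** The sentence in the Introduction also names dementia, for which a screening log and a restated target population could suffice. That is fair, and the fix below allows it. The dementia exclusion does have a measurement reason, since respondents must understand the questionnaires; the article gives none for these two.

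**Conclusion.** The concern holds in limited form. The survey row of Table 1 conflicts with the survey's aim and with its planned comparison.

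- **Prevalence** is biased downward whenever cases are excluded more often than non-cases. That condition is expected from the article's own account of severe LLD but is not quantified there. For illustration, with P = 2.8% and no non-cases excluded, losing 5%, 10% or 20% of cases gives about −5%, −10% or −20%. The bias is smaller if non-cases are also excluded. It comes on top of the 15% relative sampling error.
- **The risk model** loses the severe end of its cases and the whole dependence contrast. A history of abuse without dependence can still be compared.

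Neither loss can be repaired at analysis if people screened out are not recorded.

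**What to change.** In the survey row of Table 1 only, drop high suicide risk and lifetime dependence as exclusions and record both as variables from the screening MINI. Leave the trial row's use of these two unchanged.

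If either exclusion is kept, choose one of these:

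- log everyone screened out for it, with their MINI status for major depression, and include them in the prevalence numerator and denominator; or
- restate the target population as residents without the condition and, where dependence is the exclusion kept, drop it from the planned comparison by LLD status.

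The first option repairs prevalence but not the risk model.

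**Cost.** One table row changes, with a matching line in the analysis section. No new instrument is needed, because all 6,800 already receive the MINI. The downside is that the survey will include high-risk respondents. Under Quality Control the contingency plans are written only for carrying out the intervention, so cover for the survey cannot be assumed; the sponsor must state that those arrangements extend to it.

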### Enrollment, Supportive PDH Intervention, and Follow-Up

The 6800 community-residing elderly adults will be screened and enrolled by the investigators according to the inclusion and exclusion criteria. To ensure the balance and representativeness of sample sources, we intend to adopt a multi-stage sampling method. At the first stage, four cites will be randomly selected in Liaoning province by randomized sortition. At the second stage, one district and one township will be randomly selected from each selected city. At the third stage, one urban community and one village community will be randomly selected from each selected district/township. At the fourth stage, elderly residents will be selected from each selected urban community and village community with a convenient sampling method.The 60 community-residing elderly adults with LLD and their principle caregivers will be allocated to trial and control groups. In addition, we will ensure that there are no statistical differences between the two groups in term of the degree of depression, drug treatment programs, knowledge of mental health, geographic distribution, and other aspects before carrying out the interventions. The trial group of 30 elderly patients and their principle caregivers will receive the same content and frequency of individualized and group intervention for 6 months. By contrast, the 30 elderly patients in the control group and their principle caregivers will receive TAR, which are suitable for all MDD patients as routine. During this period, except for any additional treatment for comorbid physical diseases or short-lasting benzodiazepines for severe insomnia, other antipsychotic medications, systematic psychotherapy, and long-lasting benzodiazepines will not be allowed. The detailed content, forms, and methods of the supportive PDH intervention are listed in **Table 2**.

**Table 2 T2:** Content, form and method of supportive PDH interventions.

	Supportive PDH interventions

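### Table 1 excludes people in a current depressive episode from the survey meant to count them, and from the trial that recruits patients with MDD

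*Protocol article*

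**What the plan says.** **Survey aim.** Under Study Design: "The aim of the first stage is to investigate the epidemiological characteristics of LLD in northern China". The Objectives add "along with the prevalence, risk factors, and prevention and treatment status of LLD in Liaoning". The sample-size section sizes the survey on the prevalence of MDD. The analysis section then compares people with and without LLD and builds a structural equation model (SEM) of risk factors.

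**Survey eligibility.** The Table 1 exclusions for the 6,800 adults contain "met criteria for dementia (major neurocognitive impairment in DSM-5); in the process of a depressive episode". The enrolment section applies them at entry: "The 6800 community-residing elderly adults will be screened and enrolled by the investigators according to the inclusion and exclusion criteria".

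**Trial eligibility.** The row for the 60 LLD patients requires that they "meet diagnostic criteria for MDD without psychotic features based on the Chinese version of MINI according to DSM-IV TR". The exclusion cell of the same row contains "high suicide risk; met criteria for dementia (major neurocognitive impairment in DSM-5); in the process of a depressive episode".

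**Case definition.** The Introduction describes LLD as either a first-ever fulfilment of MDD criteria or clinically significant depressive symptoms.

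**Measurement.** The analysis section states that, among other variables, "the self-efficacy levels and depressive symptoms of the subjects will be described by frequency distribution" and other summaries, and then compares these variables by LLD status. The Data Collection section lists severity of depressive symptoms among the data gathered after enrolment. Table 3, however, assigns the GDS and the General Self-Efficacy Scale (GSES) only to the 60 patients and their caregivers.

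**The concern.** A prevalence survey has to keep the cases in both its numerator and its denominator. Here an eligibility rule applied at enrolment removes people who currently have the disorder. Applied as written, it pushes the prevalence estimate down and strips current cases from the comparison by LLD status and from the risk-factor model. These are the study's stated primary goals.

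In the trial, one row of Table 1 both requires MDD and excludes anyone now in a depressive episode. If MDD means current MDD, no patient can satisfy both. If remitted MDD is meant, the trial would test improvement in depressive symptoms among people selected for not being in an episode.

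This is not a detail that a condensed article leaves to a fuller document. The criterion is printed, twice, and nothing in the article narrows it, for instance to severe, psychotic or earlier episodes.

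**Working it through.** **1. The plan's own survey size.** Inputs from the sample-size section are P = 2.8%, two-sided α = 0.05 and margin ε = 0.15P, with N = Z²P(1−P)/ε².

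- With Z = 1.96: 3.8416 × 0.028 × 0.972 / 0.0042² = 5,927.0, so 5,928. The article states 6,179.
- With Z rounded to 2 and P = 2.8%, the result is 6,172. With Z = 1.96 and P = 2.7%, it is 6,153. Either is close to 6,179.
- 6,179 × 1.10 = 6,797, which gives the stated 6,800.

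The small mismatch does not affect this point, which concerns eligibility.

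**2. Which rate counts current cases.** The Introduction cites a meta-analysis giving point, 12-month and lifetime prevalence of 2.7%, 2.3% and 2.8%. The planning value of 2.8% matches the lifetime figure. The exclusion acts on current cases, so the point figure applies.

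| Basis | 6,800 enrolled | 6,179 analysable |
|---|---|---|
| Current cases at 2.7% | 183.6 | 166.8 |
| Lifetime cases at 2.8% | 190.4 | 173.0 |

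**3. What remains if every current case is excluded.** Taking the cited rates at face value, the share of enrolled people with lifetime but not current MDD is

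(0.028 − 0.027) / (1 − 0.027) = 0.00103, or about 0.10%.

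In 6,800 people that is 6,800 × 0.00103 ≈ 7.

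**4. Precision on that remainder.** Relative margin = 1.96 × √[(1−p)/(p·n)]. With p = 0.00103 and n = 6,179 this is about 0.78, or 78%, against the planned 15%. With so few cases the normal approximation is rough, so this is an order of magnitude.

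**5. A caution on steps 3 and 4.** The cited 12-month rate is lower than the point rate, which cannot happen within one population at one time. The three figures therefore cannot be treated as one consistent set, and the 0.1-point difference is only an illustration. The count of about 184 in step 2 does not depend on that difference.

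**6. The trial row, side by side.** Inclusion asks for MDD on the MINI. Exclusion removes current depressive episodes. The enrolment section promises balance between arms on degree of depression, the primary outcome is change in total GDS score, and the sample size is taken from before-and-after depression scores. All three presuppose patients with symptoms to improve. No passage says that the patients are to be in remission.

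**The case against.** The strongest defence is that the exclusion removes only current episodes. The MDD inclusion criterion does not contain the word current, and the Introduction's definition of LLD also admits clinically significant symptoms. Table 2 speaks of recurrence, its prevention and a rehabilitation self-help group, which fits a remitted or maintenance population to some degree. This part stands: a reader might infer that the survey would have no cases at all and the trial no eligible patients, and the document does not support that. People with past MDD, or with symptoms below an episode, could still enter. The defence does not remove the conflict, because remission is never stated and the balancing variable and primary outcome point the other way.

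A reader might also infer that the survey has no symptom score for the SEM. That goes too far, since the Data Collection section plans a severity measure after enrolment. The fault is only that Table 3 does not schedule the GDS or GSES for survey subjects.

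Nor can it be said that excluded people are already counted because Table 3 places the MINI at screening for all participants. The table's footnote defines all participants as the 6,800 survey adults, who are enrolled after the criteria are applied.

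The two exclusion cells are identical although the Participants section promises stricter criteria for the 60 patients. A copied cell is therefore a plausible explanation, but it would explain the error without correcting it.

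**Conclusion.** The point holds as an internal contradiction that must be resolved before the criteria are used. Followed as written, the survey loses its current cases: about 184 of 6,800 at the cited point prevalence. On the cited rates at face value, about 7 lifetime but not current MDD cases remain, plus an unknown number of people with symptoms short of an episode. That cannot deliver the planned prevalence estimate or support a comparison by LLD status. The direction of the bias is certain. The residual of 7 depends on rates that do not fit together, so it should be read as very few. If field staff applied the criterion only in part, the bias would again be downward, but the document gives no basis for its size.

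In the trial row, the inclusion and exclusion criteria conflict unless remitted MDD is intended, and the article does not say so.

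The Table 3 mismatch on GDS and GSES is real but secondary.

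**What to change.** - **Survey row of Table 1:** remove the current-episode exclusion, so that current cases count in the numerator and denominator of prevalence and enter the comparison by LLD status and the SEM.
- **Other exclusions related to depression, such as high suicide risk:** if they are kept, report how many people they remove, with MINI status where available, and state prevalence for the population actually covered.
- **LLD-patient row of Table 1:** the investigators should reconcile the exclusion with the MDD inclusion criterion and state which is intended. That choice is theirs.
- **Table 3:** align it with the Data Collection and analysis sections, so that the symptom-severity and self-efficacy measures planned for survey subjects are scheduled for them.

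**Cost:** an amendment to Tables 1 and 3. The eligibility change adds no procedure for enrolled people, since the MINI is already scheduled for them. Aligning Table 3 makes the survey interview slightly longer.
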